**Background and purpose of this plan**

A prospective randomized international multicenter study to compare short versus long adjuvant immunotherapy after radical surgery of stage IIb-c, III and IV cutaneous malignant Melanoma. The study is carried out in Sweden, Norway, Finland and potentially other countries will be added later on.

In order to ensure patient safety, this communication plan has been developed to describe the flow of information between the involved parties (Sponsor, Principal Investigator, and in-dependent DSMB members).

**DSMB review**

The DSMB will provide recommendations about stopping or continuing the trial based on the criteria that have been defined in the study protocol (in the case of inferiority of the experimental arm in the interim analysis or for any safety reasons affecting the risk-benefit balance). The following information should be provided to the DSMB one (1) week prior to the DSMB-meeting.

## 1. Study conduct

- a. protocol adherence (reporter protocol deviations)
- b. patient withdrawals
- c. distribution between treatment groups

## 2. Safety monitoring

- a. SAE:s and SUSAR:s
- b. New information that has been published if applicable
- c. The results of the interim analysis (done when approximately two-thirds of the total number of planned subjects are enrolled)

However, the DSMB may for any concerns regarding safety recommend stopping the trial.

It is the responsibility of the Sponsor, based on the advice provided by the DSMB, to decide whether a premature end of the study will be made.

## **Schedule**

DSMB members will be called for meetings in the following cases:

- Close to FPI for an initial meeting
- Once a year while the study is ongoing.
- Immediately after finalisation of the interim analysis.
- At any time when safety issue occurs and upon the Principal Investigator's demand.

## **Attendance**

At least one of the independent members should attend the official DSMB meeting.

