### **11.1 SAMPLE SIZE CALCULATIONS (CO-PRIMARY ENDPOINT – DISTANT METASTASES FREE SURVIVAL (DMFS) AND RELAPSE FREE SURVIVAL (RFS))**

The study design is a non-inferiority trial investigating whether short-term adjuvant immunotherapy, is non-inferior to long-term adjuvant immunotherapy (standard of care) with a non-inferiority margin (4.0%) being accepted as being clinically appropriate in this study population.

Assumptions for the sample size calculation:

- DMFS at 2 years was 88.1% for stage IIb-c patients (Keynote 716 study) (1)
- DMFS at 2 years was 70% for stage III-IV patients (Checkmate 238 trial) (2)
- DMFS for the sample size will be based on these two measurements with a conservative estimate of 75.0% at 2 years and assuming same rates for RFS.
- Power = 80%
- Alpha level = 5%
- Non-inferiority Margin = 4%
- Accrual time = 48 months
- Follow up time = 60 months

Assuming a 4-year accrual and 5-year follow-up duration, a sample size of 1872 patients (936 in each study arm) will have 80% power (90% for each endpoint, which corresponds to a total power of 81%) with one-sided 95% confidence to declare non-inferiority with a margin of 4.0% (i.e., from 75% to 71.0% in the observation group) based on a 1:1 randomization with a corresponding HR of

1.19. The sample size may be either re-estimated or the non-inferiority boundary adjusted if the number of patients lost to follow-up is of concern.

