## 11.3 INTERIM ANALYSIS

If we allocate  $\alpha = 0.005$  to the interim analysis and  $\alpha = 0.045$  to the final analysis then the total sample size would increase from 1872 to 1880 subjects (940 in each arm). The calculation was made using the O'Brien-Fleming Boundary. The interim analysis will be conducted when approximately two-thirds of the total number of planned subjects are enrolled which is the optimal timing when using the O'Brien-Fleming Boundary for both co-primary endpoints (12). The results of the interim analysis will be carefully assessed by the Data safety monitoring board (DSMB) without delay and in the case of inferiority of the experimental arm the study will be prematurely terminated and all sites informed.

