## **Meeting minutes**

Minutes of all official meetings of the DSMB will be part of the Sponsor's trial master file.

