## **Meeting preparation and plan**

- Investigator(s) is responsible to collect all relevant information and safety data, and submit the data to Sponsor.
- The Sponsor or project manager distributes the prepared material (as described under DSMB review) to DSMB members 1 (one) week prior to the meeting, and calls for a meeting.
- DSMB members meet on-line, by telephone or in person and discuss the data, meeting minutes will be written and filed.
- A recommendation to continue or stop the trial will be made during or after the meeting by the independent DSMB members.

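### The DSMB charter puts no firewall between the sponsor and the by-arm interim results, and its attendance minimum of one independent member is weak for the only efficacy interim

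*Protocol*

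**What the plan says.** Appendix 2 states that its purpose is to set out how information passes between the sponsor, the principal investigator and the independent board members. It does so as follows.

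- **Content of the package.** Under Safety monitoring, the material for the board includes "The results of the interim analysis (done when approximately two-thirds of the total number of planned subjects are enrolled").
- **Who handles it.** Under Meeting preparation and plan: "Investigator(s) is responsible to collect all relevant information and safety data, and submit the data to Sponsor". Then: "The Sponsor or project manager distributes the prepared material (as described under DSMB review) to DSMB members 1 (one) week prior to the meeting".
- **What the interim tests.** Section 11.3 says that "in the case of inferiority of the experimental arm the study will be prematurely terminated and all sites informed". The charter's DSMB review paragraph uses the same criterion, alongside safety.
- **Attendance.** "At least one of the independent members should attend the official DSMB meeting". The organisation table appears to list three independent members. Above them it lists the principal investigator, site investigators, a sponsor representative, project managers and a biostatistician.
- **Minutes.** "Minutes of all official meetings of the DSMB will be part of the" sponsor's trial master file. No open and closed parts are distinguished, and no embargo is set.
- **Confidentiality.** One general sentence makes everything discussed at meetings confidential. It does not say from whom.
- **Safeguards present.** The independent members make the recommendation (Meeting preparation and plan). Section 13.2 has the committee appointed from outside those running the study.

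**The concern.** The usual reason for having a monitoring board is that those who run a trial stay unaware of the accumulating comparison. Here the stated route for the interim results runs through the sponsor's hands before the independent members receive them, and the minutes come back to the sponsor's file.

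Four features of this trial make that matter more.

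- The arms differ in duration (6 versus 12 months) and no placebo is described, so treatment is in effect open-label.
- After baseline, compulsory imaging falls only at 6 and 24 months, and extra work-up for suspected relapse is left to the investigator's judgement (Study Follow-up Scheme). Both primary endpoints, DMFS and RFS, depend on when relapse is looked for.
- The primary efficacy analysis is per-protocol (section 11), so a shift in adherence changes who is analysed.
- Section 11.1 adds that "The sample size may be either re-estimated or the non-inferiority boundary adjusted" if loss to follow-up becomes a worry, without a threshold. If the sponsor has had the interim result, nobody could show that such a change was made blind to it.

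**Working it through.** The point is mainly textual; the arithmetic only shows how much of the trial would still lie ahead.

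**Step 1. Are the interim results comparative?** The protocol does not use that word. But both section 11.3 and the charter make inferiority of the experimental arm the stopping criterion. Inferiority cannot be judged without comparing the arms, so the results must be by arm.

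**Step 2. Who holds them, and when?** Safety monitoring puts the interim results in the package. Meeting preparation and plan says the sponsor or project manager distributes the package described under DSMB review, one week ahead. Safety monitoring is part of that description. Read together, the sponsor side has the results at or before the time the board does.

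**Step 3. Does anything else close the route?** The charter mentions no closed report, no closed session and no direct line from a statistician to the independent members. The confidentiality sentence covers what is discussed at meetings and excludes neither sponsor nor investigators. The minutes rule covers all official meetings.

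**Step 4. Attendance.** One independent member out of an apparent three meets the charter's minimum. No other participation rule is given for the interim.

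**Step 5. What remains after the interim?**

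Inputs from the protocol: 1,880 patients and an interim at about two-thirds enrolment (section 11.3); 48 months of accrual, 60 months of follow-up and 75% event-free at 2 years (section 11.1). Assumptions: exponential event times, uniform accrual, no dropout, and the same rate in both arms.

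- Enrolled at the interim: 1,880 × 2/3 = 1,253, at month 48 × 2/3 = 32. Still to enrol: 1,880 − 1,253 = 627.
- Two-year events in all: 1,880 × 0.25 = 470.
- Patients with a full 24 months by month 32 were enrolled in months 0 to 8: 1,880 × 8/48 = 313. Events: 313 × 0.25 = 78.
- The other 1,253 − 313 = 940 have between 0 and 24 months of follow-up. Their mean event probability is 1 − (1 − 0.75)/(−ln 0.75) = 1 − 0.25/0.2877 = 0.131. Events: 940 × 0.131 = 123.
- Two-year events by the interim: 78 + 123 = 201, and 201/470 = 43%. Still to come: 57%.

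Counting all events instead of only those within two years, with rate λ = −ln(0.75)/24 per month:

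- By the interim: mean event probability 1 − (1 − e^(−32λ))/(32λ) = 0.169, so 1,253 × 0.169 = about 212 events.
- By month 108 (48 + 60): mean event probability 1 − (e^(−60λ) − e^(−108λ))/(48λ) = 0.630, so about 1,184 events.
- 212/1,184 = 18%. Still to come: 82%.

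So between 57% and 82% of events lie after the interim, depending on which events are counted.

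**The case against.** The strongest reply is that the charter already protects independence where it counts. The recommendation belongs to the independent members, they come from outside the study team, and discussions are confidential. That stands as far as it goes. A reader might infer from the routing and the attendance rule that the board is not independent, and the text does not support that. These safeguards govern who advises, though, and leave open who sees the data.

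Other stronger readings also go beyond the documents:

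- **That one member can settle the recommendation.** The attendance sentence sets a minimum presence and is not a voting rule. The recommendation may come after the meeting and is attributed to the independent members in the plural. The count of three comes from a list that may change.
- **That recruiting sites will know the interim hazard ratio.** Investigators send data to the sponsor; nothing says that results go back to sites. Investigator roles stand in the organisation table, but nothing says they receive the interim results.
- **That the sponsor may move the margin on the interim result.** Section 11.1 ties any change to loss to follow-up and names no decision-maker. Section 15.3 requires approval for substantial modifications.
- **That the sponsor's final say on stopping is a fault.** A sponsor deciding on the board's advice is usual. So is keeping minutes in the trial master file; only the lack of a closed part or an embargo is at issue.

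Finally, the shares of patients and events still to come measure exposure and do not measure bias.

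**Conclusion.** The point holds as a gap in the information route. As written, Appendix 2 gives the sponsor or project manager the by-arm interim results, sets aside no closed minutes, and excludes neither sponsor nor investigators through its confidentiality sentence. The sponsor, and possibly trial staff named in the organisation table, could know the comparison with about one third of patients (627 of 1,880) still to be enrolled. Under the assumptions shown, 57% of the 2-year events would still be to occur, or 82% of all events over the full follow-up. That knowledge could affect recruitment, adherence and relapse work-up, and would leave any later change of size or margin open to challenge. The documents do not allow the resulting bias to be quantified.

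The attendance minimum is a secondary weakness: one independent member is thin for the only planned efficacy interim.

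The conclusion rests on two inferences: that an interim judging inferiority must be comparative, and that distributing the package implies access to it. The change should be made before the interim, because unblinding cannot be undone.

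**What to change.** Amend Appendix 2 in four places.

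1. **Meeting preparation and plan.** The statistician who runs the interim sends the by-arm results directly and only to the independent members, for a closed session. The sponsor or project manager continues to distribute the remaining material.
2. **DSMB review.** After the interim the sponsor receives only the recommendation to continue or stop. By-arm results are released to it only if stopping is recommended.
3. **Meeting minutes.** Split minutes into open and closed parts. Open minutes are filed as now; closed minutes are withheld from the sponsor until the trial ends.
4. **Attendance.** A majority of the independent members, for example two of three, must take part in the interim recommendation.

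This is charter wording. It changes no endpoint, sample size or patient's treatment. The cost is slightly harder scheduling and keeping the interim statistician out of decisions on trial conduct. The biostatistician already listed could fill that role. If that person also advises on conduct, a second statistician would be needed for the interim, a real though small expense in a trial that expects no industry funding (section 13.3).

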## **Meeting minutes**

Minutes of all official meetings of the DSMB will be part of the Sponsor's trial master file.

## **Confidentiality**

All information discussed during DSMB meetings should be treated as confidential.

## **Meeting preparation and plan**

- Investigator(s) is responsible to collect all relevant information and safety data, and submit the data to Sponsor.
- The Sponsor or project manager distributes the prepared material (as described under DSMB review) to DSMB members 1 (one) week prior to the meeting, and calls for a meeting.
- DSMB members meet on-line, by telephone or in person and discuss the data, meeting minutes will be written and filed.
- A recommendation to continue or stop the trial will be made during or after the meeting by the independent DSMB members.

## **Other related actions**

If an SAE is classified as a SUSAR (Suspected Unexpected Adverse Reaction), the sponsor will report it to the authorities (within 7 days if life-threatening or death, or within 15 days if not life-threatening).

- Depending on the nature of the safety information, and if, in the opinion of the Investigator, the event may contribute to the safety evaluation for future treatment, the Investigator and Sponsor may at any time have an on-line, telephone or face-to-face meeting with the DSMB for advice regarding safety issues. Relevant parties (e.g., Project Manager) are invited to discuss safety issues to ensure that essential safety information is shared within the study team. The meetings will be documented and archived in the Trial Master File.
- Once a year a Development Safety Update Report (DSUR) will be compiled by the Sponsor with the help of the Project Manager at KFUE and submitted to the regulatory authorities.
